## Abstract

**Background:**

Therapeutic exercises that help reduce stress and anxiety, both mentally and physically, are called relaxation techniques. In order to ascertain the benefits of the two relaxation techniques on pain, urine incontinence, sleep quality, and activities of daily living, this study will compare them with the conventional physiotherapy exercise in lower segmental cesarean sections (LSCS).

**Methods:**

Forty-six LSCS subjects with pain, urine incontinence, sleep quality, and activities of daily life will participate in a comparative study that is a blinded (statistical) analysis. The participants will be divided into two groups following randomization: (1) Benson’s relaxation and (2) Mitchell’s relaxation, and both groups will receive exercises from conventional physiotherapy. Every group will go through the initial evaluation and a post-intervention assessment.

**Discussion:**

This study is anticipated to improve pain, urinary incontinence, sleep quality, and activities of daily living following a lower segmental cesarean section. Following the completion of the study, the data will be published. If the benefits are demonstrated, Benson’s or Mitchell’s relaxation approach is used in conjunction with conventional physiotherapy exercises after lower-segmental cesarean sections.

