## Objectives {7}

The study aims to compare Benson’s relaxation (group A) and Mitchell’s relaxation (group B) along with conventional physiotherapy exercises in both groups to evaluate the pain, urinary incontinence, improving the sleep quality and activities of daily living in LSCS subjects with the help of outcomes to determine which group has better improvement.

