### Intervention description {11a}

#### Conventional physiotherapy exercise

Patients who meet the inclusion criteria will be selected following ethical clearance from the Institutional Ethical Committee.

Pretreatment and post-treatment data will be recorded with the help of outcome measures. After dividing patients into two groups, each group A and B will receive Mitchell’s relaxation and Benson’s relaxation, respectively, for 30 min along with breathing exercises; followed by this, patients will receive interventions 5 days a week. This relaxation would be given with conventional physiotherapy exercises in both groups. Intervention will be given on POD-2 after LSCS in both the groups A and group B.

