## Data collection and management

### Plans for assessment and collection of outcomes {18a}

Baseline assessment: Before giving any intervention, data will be collected from subjects at the beginning of the first week.Intervention period: During the 4 weeks of the intervention, subjects will get both the relaxation technique (Benson’s and Mitchell’s), along with the conventional physiotherapy exercises.Post-intervention assessment: After the fourth week of intervention, right after the intervention period, data will be gathered once again.

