#### Comparisons within the group (before and after the intervention)

If the data are normally distributed, the paired *t*-test will be employed.

If the data are not normally distributed, the Wilcoxon signed-rank test will be applied.

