There are various reasons why the study is important. It begins by directly contrasting two popular but little-studied relaxation methods in a group of women who are at a heightened risk of postpartum problems. Second, the study mirrors actual clinical practice by combining these methods with traditional physiotherapy, and it may help shape evidence-based recommendations for LSCS recovery. Third, a randomized, single-blind methodology and verified outcome measures improve the findings’ generalizability and dependability. In order to improve pain management, urinary continence, sleep quality, and everyday functioning for women following LSCS surgery, the study may encourage the wider use of relaxation techniques in post-cesarean physiotherapy protocols if the results show a substantial advantage. By treating the psychological as well as the physical components of healing, this would constitute a significant advancement in postpartum treatment and eventually improve the quality of life for this patient population. The limitation of this study is that it effectively compares the two relaxation techniques; the absence of a third arm receiving conventional physiotherapy alone limits the ability to determine the absolute additive benefit of either relaxation technique over standard care.

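### The abstract announces a comparison with conventional physiotherapy, and adoption if benefit is shown, but the two-arm design can only compare Benson's with Mitchell's

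*Protocol article*

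**What the plan says.** Two statements in the abstract of the protocol article concern benefit over physiotherapy.

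- Background, on how the benefits of the techniques will be established: "this study will compare them with the conventional physiotherapy exercise in lower segmental cesarean sections (LSCS".
- Discussion, on what follows from the result: "If the benefits are demonstrated, Benson’s or Mitchell’s relaxation approach is used in conjunction with conventional physiotherapy exercises after lower-segmental cesarean sections".

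The rest of the article describes a different contrast.

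- Abstract, Methods, lists the groups: "1) Benson’s relaxation and (2) Mitchell’s relaxation, and both groups will receive exercises from conventional physiotherapy". The Intervention description {11a} also gives physiotherapy to both arms.
- Objectives {7} sets a technique-against-technique aim: "to determine which group has better improvement".
- Statistical methods {20a} has one between-group comparison, Mitchell's against Benson's (independent t-test or Mann–Whitney). It also plans before/after tests within each group: a paired t-test or, failing normality, "If the data are not normally distributed, the Wilcoxon signed-rank test will be applied".
- The main Discussion states as a limitation that "the absence of a third arm receiving conventional physiotherapy alone limits the ability to determine the absolute additive benefit".

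On timing, Intervention description {11a} says "Intervention will be given on POD-2 after LSCS in both the groups A and group B", and Plans for assessment {18a} says of the baseline: "Before giving any intervention, data will be collected from subjects at the beginning of the first week". The only later assessment follows the fourth week of intervention.

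**The concern.** A comparison with physiotherapy needs a group that receives physiotherapy alone, and there is none. The randomised contrast can rank the two techniques. Even a clear difference between them would not show that either one adds anything to physiotherapy: the better technique could be useless and the other harmful, or both could help. The abstract therefore announces a question, and a practice consequence, that the design does not address.

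The within-group tests make this more than a matter of phrasing. They sit beside the between-group tests under the methods for primary and secondary outcomes, and nothing says what they are for. A reader who looks for the analysis that shows the benefit mentioned in the abstract will find only these tests to point to. They measure change from before the intervention, given on postoperative day 2, to the end of week 4. Women recovering from surgery, doing physiotherapy and taking routine postpartum medication (permitted under {11d}) can be expected to improve over that period whatever the relaxation technique does. At stake is a recommendation to add relaxation to standard care that rests on change which cannot be attributed to relaxation.

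**Working it through.** **1. What the trial is sized for.** The inputs are in Sample size {14}: means 7.916 and 5.983 (difference 1.933), SDs 2.256 and 2.327, two-sided alpha 0.05, power 0.80, ratio 1:1.

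n per arm = (1.960 + 0.842)² × (2.256² + 2.327²) / 1.933² = 22.07, rounded up to 23 per arm and 46 in total.

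The stated 46 is reproduced. (The section prints 0.084 for the power quantile. Taken literally that would give 12 per arm, so it is a misprint for 0.84 and does not change the stated size.) With 23 per arm the power is 0.816 by the normal approximation and 0.799 by the t distribution. The formula is the one for two independent means, so the trial is sized for a between-group contrast.

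**2. Which contrasts the design contains.**

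| Question | Analysis planned | Can the design answer it? |
|---|---|---|
| Benson's vs Mitchell's, each with physiotherapy | Independent t-test / Mann–Whitney | Yes, randomised |
| Either technique with physiotherapy vs physiotherapy alone | None | No, no such arm |
| Before vs after within one arm | Paired t-test / Wilcoxon | Measures change, not its cause |

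The abstract's Background claims the second row. The Objectives and the between-group test give the first.

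**3. What the paired test does when the technique does nothing (illustration).** From the documents: n = 23 per arm and a common SD of √[(2.256² + 2.327²)/2] = 2.292. Assumed, because the documents give neither: the natural fall m in VAS and the pre/post correlation ρ. The value m = 1.933 is the planning difference borrowed as a scale; it is not a recovery figure from the protocol.

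SD of change = 2.292 × √[2(1 − ρ)]; noncentrality = m / (SD of change / √23); 22 degrees of freedom, two-sided 0.05.

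For m = 1.933:
- ρ = 0: SD of change 3.241, standard error 0.676, noncentrality 2.86.
- ρ = 0.7: SD of change 1.775, standard error 0.370, noncentrality 5.22.

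Probability that one arm's paired t-test is significant with zero technique effect:

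| Natural fall (VAS) | ρ = 0 | ρ = 0.3 | ρ = 0.5 | ρ = 0.7 |
|---|---|---|---|---|
| 0.5 | 0.109 | 0.135 | 0.170 | 0.253 |
| 1.0 | 0.293 | 0.394 | 0.516 | 0.733 |
| 1.933 | 0.780 | 0.904 | 0.971 | 0.999 |
| 3.0 | 0.989 | 0.999 | 1.000 | 1.000 |

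The arms are independent, so the probability that both are significant is the square: 0.61 to 0.998 at a fall of 1.933. With equal recovery and no technique effect in either arm, the between-arm test rejects with probability 0.05 in every cell.

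**The case against.** The body of the article is largely sound. The objective is a comparison of the two techniques, the trial is sized for two independent means, a direct randomised test is planned, and natural recovery does not bias that test. The missing arm is openly stated as a limitation. The abstract's own Methods paragraph describes the arms correctly, so a careful reader of the abstract alone can see that there is no control group. The adoption sentence names one technique or the other, which can be read as whichever proves better. Reporting paired tests beside a between-group test is not in itself an error.

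All of this stands, and it limits what can be said. A reader might infer three stronger things, none of which the documents support:

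- **That the before/after tests decide whether there is benefit.** No section says so. The adoption sentence does not name a deciding analysis.
- **That the better technique will be picked by setting a significant result in one arm against a non-significant one in the other.** No such reasoning is planned; a direct comparison is specified.
- **That the trial will almost surely find improvement in both arms and recommend relaxation on no evidence.** The planned randomised test is evidence on relative effect, and the probabilities above depend on an assumed recovery and correlation. They are modest for a fall of 1 point or less, and only VAS was examined.

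The objection does not remove the conflict between the abstract and the body. A limitation stated near the end of the Discussion does not correct an abstract that claims the comparison, and neither reading of the adoption sentence gives evidence of benefit over physiotherapy.

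**Conclusion.** The point holds as an internal contradiction with a consequence for interpretation. The abstract's Background and Discussion conflict with the abstract's Methods, the Objectives, the single between-group test and the stated limitation. The within-group tests cannot bridge the gap, and the protocol leaves their role undefined.

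The contradiction and the impossibility of attributing before/after change to the technique need no numerical assumption. The size of the possible misreading does. At an assumed natural fall of 1.933 points and a correlation of 0 to 0.7, an inert technique would show a significant before/after change in a given arm with probability 0.78 to 0.999; at 1 point, 0.29 to 0.73. These figures illustrate the mechanism and are not a forecast. The randomised comparison of Benson's with Mitchell's is valid for relative effect and is not called into question here.

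**What to change.** 1. Reword the abstract's Background and Discussion so that the question is Benson's versus Mitchell's, each added to conventional physiotherapy.
2. State in Statistical methods {20a} that conclusions rest only on the between-group difference, and that any recommendation concerns the choice between the two techniques, not benefit over physiotherapy alone.
3. Label the within-group changes as descriptive and report them as mean change with a 95% confidence interval.

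No arm, participant or measurement is added. The cost is some rewording and a narrower stated conclusion: the trial could no longer be presented as showing that relaxation adds to standard care.

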**Result:**

The protocol would be given for 4 weeks. The initial assessment would be conducted before the intervention, and the post-assessment would be performed after the completion of the 4 weeks of intervention.

**Trial registration:**

Trial REF/2025/03/102462, Registration number- CTRI/2025/04/085318. Date of registration-22/04/2025.

## Introduction

### Background and rationale {6a}

The rate of cesarean sections has dramatically increased globally in recent years. Two types of cesarean section are performed: elective and emergency cesarean section [1]. Women undergo a number of physiological, psychological, and social changes during the postpartum phase [2]. These changes result in a number of issues that impact women’s daily lives. Following a cesarean section, women seem to be more susceptible to sleep disturbances. This discrepancy is particularly noticeable in late pregnancy and the early postpartum period, which has been identified as a time of vulnerability to sleep problems [3]. A loss of bladder control known as urinary incontinence can range from a minor leak of pee following coughing, sneezing, or laughing to an absolute inability to control urination. Urinary incontinence is most common in women during pregnancy and after giving birth [4]. One of the most prevalent issues in the postpartum phase is back discomfort. Seven out of ten women who give birth have back pain, which is more than 70% of cases, according to statistical evidence. Obesity, poor posture, sitting, walking, and standing are all associated with postpartum back pain. According to the study’s findings, post-anesthesia back discomfort can be reduced by practicing posture correction, yoga, meditation, lumbar support, rest, and massage [5].

Therapeutic exercises that help reduce stress and anxiety both mentally and physically are known as relaxation techniques [6]. Relaxation techniques can also be used as adjunctive therapies in a range of healthcare settings to treat patients with a variety of diseases, mostly but not exclusively stress, anxiety, depression, and pain [7]. Psychophysiological therapies such as relaxation techniques reduce stress by encouraging mental and physical relaxation [8]. These methods effectively lessen pain and anxiety and are frequently used in physiotherapy [9]. A clear description of therapeutic relaxation appears challenging, even though relaxation is a widely recognized and frequently utilized term [10].

Mitchell’s method is a silent, solitary aural relaxing technique. In addition to including deep breathing, relaxation techniques, and guided imagery, it highlights the mind–body psychoneuroimmunological relationship and suggests total involvement and autonomy. It is theorized that the posture associated with stress causes the neurological and endocrine systems to change, increases muscle tension, and encourages muscular stiffness and dystonic patterns [11].

Benson’s relaxation technique was developed by Herbert Benson in 1970 as a straightforward method of stress relief [12]. The quality of sleep, general quality of life, and pain intensity all improved as a result of this tactic. At the same time, it promoted physical activity and reduced mood disorders and anxiety [13]. Crucially, Benson’s relaxation method has no negative effects on people, offers a number of advantages, and is easy to apply [14].

## Objectives {7}

The study aims to compare Benson’s relaxation (group A) and Mitchell’s relaxation (group B) along with conventional physiotherapy exercises in both groups to evaluate the pain, urinary incontinence, improving the sleep quality and activities of daily living in LSCS subjects with the help of outcomes to determine which group has better improvement.

## Trial design {8}

It will be a quantitative, analytical, comparative study with a single-blinded study design, meaning that participants will be blinded. We conducted this protocol in accordance with SPIRIT (Standard Protocol Items: Recommendation for Interventional Trials).

Before randomization, consent forms will be used to get written informed consent from each participant.

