##### Group A

Subjects will receive 30 min Mitchell’s relaxation exercise per day, along with conventional physiotherapy exercises in both groups. Follow-up of the patient will be done daily. Diaphragmatic breathing exercises and a series of serial isotonic contractions aimed at reciprocal inhibition are both components of Mitchell’s physiological relaxation technique.

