### Strategies to improve adherence to interventions {11c}

Education and demonstration of participants: At the beginning of the study, participants will get explicit written and verbal instructions along with examples of the designated physiotherapy exercises and relaxation techniques. This guarantees that participants comprehend the processes and their significance.Supervised sessions: To guarantee proper technique and promote participation, interventions will be given or overseen by a principal investigator while the participants are in the hospital.

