## Assignment of interventions: blinding

### Who will be blinded {17a}

Outcome accessor would be blinded to the intervention.

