#### Rationale

Using established questionnaires and scales, the methodology of this protocol only focuses on clinical and patient-reported outcomes, including pain, urinary incontinence, sleep quality, and activities of daily life.

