## Discussion

In order to assess the efficacy of Benson’s and Mitchell’s relaxation techniques, each in conjunction with conventional physiotherapy, for women recovering from lower segmental cesarean sections (LSCS), the protocol offers a carefully planned, single-blind, randomized comparative clinical trial. This study’s justification stems from the high and increasing prevalence of LSCS worldwide, which is linked to serious postpartum problems such as pain, urinary incontinence, sleep issues, and diminished capacity to carry out everyday tasks. Comprehensive rehabilitation is necessary since these issues affect not only physical healing but also psychological and social well-being.

Both Mitchell’s and Benson’s relaxation methods are well-researched psychophysiological therapies that have been demonstrated to enhance sleep quality and lessen stress, pain, and anxiety in a variety of populations. Nevertheless, there is a dearth of direct comparison data about their efficacy in LSCS patients. In order to fill this gap, the procedure enlists 46 women between the ages of 20 and 40. They are then randomly randomized to receive either Benson’s or Mitchell’s relaxation technique in addition to conventional physiotherapy exercise. Five days a week, for 30 min per session, the interventions are given under supervision to guarantee proper technique and adherence. This strategy minimizes confounding variables while enabling a strong comparison.

The visual analogue scale (VAS) for pain, the incontinence severity index (ISI) for urine incontinence, the Pittsburgh Sleep Quality Index (PSQI) for sleep quality, and the Barthel Index for activities of daily living are among the extensive and validated outcome measures used in this study. These instruments will be employed both before and after the intervention, allowing for a comprehensive evaluation of the methods’ effects on important facets of postpartum recuperation. Careful attention is paid to ethical issues: all participants provide their informed consent, and precise inclusion and exclusion standards are set up to guarantee participant security and data integrity. Both procedures are safe and non-invasive, and the protocol permits stopping them if there is any discomfort or unfavorable outcome. Education, demonstration, and supervised sessions are some strategies to increase adherence, which are essential for guaranteeing consistent implementation of the interventions and trustworthy outcomes.

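### The protocol's statements on who is blinded do not agree, and participant blinding cannot hold for technique, so both primary outcomes and the PSQI are unmasked self-reports

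*Protocol article*

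**What the plan says.** The protocol article describes blinding in several places:

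- Abstract, Methods: a "comparative study that is a blinded (statistical) analysis".
- Trial design {8}: a "single-blinded study design, meaning that participants will be blinded".
- Who will be blinded {17a}: "Outcome accessor would be blinded to the intervention". No other party is listed.
- Discussion: a "single-blind, randomized comparative clinical trial", with no party named. Later it states that "a randomized, single-blind methodology and verified outcome measures improve the findings’ generalizability and dependability".

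On what participants experience, Strategies to improve adherence {11c} says that "participants will get explicit written and verbal instructions along with examples of the designated physiotherapy exercises and relaxation techniques". Sessions last 30 minutes, 5 days a week ({18b}), over 4 weeks ({18a}).

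On the outcomes, Outcomes {12} makes VAS and ISI primary, and PSQI and the Barthel Index secondary. The rationale under {33} says the protocol "only focuses on clinical and patient-reported outcomes".

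**The concern.** A single-blind design, as {8} defines it, masks the participants. The section meant to settle the question names someone else. Trial staff cannot tell which statement to follow, and the rule in {17b} against any unblinding has no clear object until the blinded party is fixed.

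The second difficulty is more serious. The party named in {8} is the one who learns and performs the intervention, and who also supplies most of the outcome data. If the trial is reported as the protocol describes it, pain, incontinence and sleep ratings will be presented as blinded when they come from women who know their technique. Readers judging risk of bias would be misled on both primary outcomes.

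**Working it through.** The only arithmetic here is a count, so the check sets the sections side by side.

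**1. Do the statements agree?**

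| Section | Party said to be blinded | Compatible with {8}? |
|---|---|---|
| Trial design {8} | participants | – |
| Who will be blinded {17a} | outcome assessor | no |
| Abstract, Methods | statistical analysis | no |
| Discussion | none named | cannot be judged |

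The second and third rows are compatible with each other, since one trial can mask both assessor and analyst. The clash is between those two and {8}, where single-blind is defined as masking participants. The person described as blind in Implementation {16c} only creates the random sequence and is not a further masked role.

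**2. Can participants be blinded to technique?**

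- Under the Group A heading, Mitchell's technique consists of "Diaphragmatic breathing exercises and a series of serial isotonic contractions aimed at reciprocal inhibition". Under the Group B heading, Benson's technique consists of a quiet setting, a restful position, muscle relaxation from feet to face, and attention to breathing. The two are recognisably different activities.
- Each woman is instructed in her technique verbally and in writing, with examples ({11c}).
- The schedule gives 5 sessions a week × 4 weeks = 20 sessions. At 30 minutes each, 20 × 30 = 600 minutes, or 10 hours of practice.
- No sham procedure, disguised technique or masking of the study hypothesis is described.

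A woman in this trial therefore knows which activity she performs.

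**3. Does a blinded assessor protect the outcomes?**

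| Outcome | Role | Source of the rating |
|---|---|---|
| VAS | primary | the woman's rating of pain |
| ISI | primary | questionnaire on incontinence |
| PSQI | secondary | respondent rates her own sleep |
| Barthel Index | secondary | rater not stated |

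For the first three rows the judgement originates with the woman, whoever hands out or scores the form. That is 3 of 4 outcomes, including both primaries. Assessor masking could protect the Barthel Index if an assessor rates it, but the protocol does not say.

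**4. Who else knows the allocation?** The principal investigator enrols and assigns participants ({16c}), and gives or oversees sessions during the hospital stay ({11c}). That person cannot also be the blinded assessor of {17a}, so a separate assessor is already implied.

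**The case against.** Several points on the other side are fair, and they limit what can be claimed.

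- A reader might infer three mutually contradictory statements. That overcounts: masking the assessor and masking the analysis fit together, and only {8} is out of line with them.
- A reader might infer that no participant blinding of any kind is possible. The documents do not support that. Both arms are active and share the same session length and conventional physiotherapy, so women could be kept unaware of the other technique's content or of any expected superiority. The consent pages are not in the text, so what women are told cannot be checked. What stands is that they cannot be blinded to the technique they perform, and that {8} claims blinding without this limit.
- Self-completion of VAS and ISI is inferred from the type of instrument and the reference to patient-reported outcomes. The mode of administration is not stated. The inference is reasonable, but it is an inference.
- A reader might infer a definite bias towards one arm, or attach a percentage to it. Only a difference in expectation between the two arms would bias the comparison. The protocol describes both techniques as beneficial ({6b}), and its objective favours neither. It gives no figure for expectation bias, so any share of the planned VAS difference would rest on an invented number.
- Investigator supervision is stated only for the hospital stay, so it should not be read as covering all 4 weeks.

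It is also true that unblinded participants are inherent in comparing two taught techniques. That excuses the design but not its description.

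**Conclusion.** The point holds in this form. The blinded party in {8} does not match {17a} or the abstract. Participant blinding to technique is a stated design property that the trial, as described, does not have. Both primary outcomes and the PSQI are in effect unmasked self-reports, and the Discussion's use of single blinding as a reason for confidence is unsupported for them.

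The size is 3 of 4 outcomes affected; the magnitude and direction of any resulting bias are unknown. The conclusion assumes that VAS, ISI and PSQI record the woman's own judgement, and that no sham or hypothesis masking exists beyond what the article describes. The sample size and the planned tests are not affected.

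**What to change.** - Use one statement in the abstract, {8}, {17a} and both places in the Discussion: participants and the treating investigator are not blinded to technique; the outcome assessor already planned in {17a} and the statistician are masked to group.
- Mask the statistician with neutral codes, not A and B. Those letters are published as named treatments, and their meaning is reversed between Objectives {7} (Benson's as A) and Intervention description {11a} with the Group A and Group B headings (Mitchell's as A). These sections must be reconciled in any case.
- Have VAS, ISI and PSQI collected without the treating investigator present, and state how each is administered and who rates the Barthel Index.
- Give participants neutral information about the two techniques, with no suggestion of which is expected to do better.
- In the Discussion, describe VAS, ISI and PSQI as self-reports unmasked to technique, and stop citing single blinding as a strength for them.

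The cost is protocol wording, a coded dataset and some care over who is present at assessment. No additional role is needed if the assessor in {17a} is, as implied, separate from treatment. The downside is that the stated level of blinding becomes less favourable.
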